### Decision rules

2.7

Participants will access the microinterventions through push notifications sent via the study mobile phone application, following a predefined time-based sequence (See Fig. 2).

**Fig. 2 fig2:**
[figure not shown]
Schedule of microinterventions. Abbreviations: FR: Friendly reminder

The 50th birthday party microintervention will be sent on the first day after downloading the app, and it will be sent only once with the following message: “It's time to start the journey! Listen to your first visualization”*.* When participants enter the app, this module will be named “Starting your journey!” and will remain available for the next 24 h. Throughout the day, participants will receive two reminders if the strategy has not been completed. The first reminder will be sent at 3:00 p.m. with the message: “Don't forget your first notification! It's really important to us that you complete it”. The second reminder will be sent at 9:00 p.m. with the message: “To stay in the study, please complete today's notification. We'd love to keep you on board!”

The 3-min wake-up microintervention will be sent daily in the morning during the 6 days following the initial microintervention, with the message: “Time for a quick exercise! It will disappear at 12:00 p.m.” When participants enter the app, this module will be named “Before starting your day!” and will be available from 6:00 a.m. to 12:00 p.m. Reminders will be sent at 9:00 a.m. and at 11:00 a.m. with the following messages, respectively: “Don't miss your morning check-in! It takes less than 5 min – Available until 12:00!” and “Don't forget about me! Morning notification disappears in 1 h”

The friendly reminder microintervention will be sent three times per day and will be available from 3:00 p.m. to 5:00 p.m., from 6:00 p.m. to 8:00 p.m., and from 9:00 p.m. to 11:00 p.m., on the same days as the morning notifications They will appear with the message: “Just 1 question”.

### Procedure

2.8

Interested participants will access it through a link or QR code provided in the advertisements. The study will comprise 4 steps. In Step 1, students will begin by completing an initial web-based survey on Qualtrics. This survey will provide detailed information about the study and include the informed consent form. To minimize response bias, the specific research questions and hypotheses will not be disclosed during participation. The survey will also collect sociodemographic and clinical data, as well as responses to baseline validated questionnaires. Sociodemographic data will include age, gender identity, marital status, education level, nationality, and university enrollment. Clinical data will include information on whether participants are currently receiving psychiatric or psychological treatment for a specific mental disorder and whether they have been professionally diagnosed with a severe mental disorder. Participants who do not meet the eligibility criteria will be excluded due to the emotional sensitivity that the interventions might elicit and the absence of therapist guidance, which could increase the risk of iatrogenic effects. These participants will receive an email thanking them for their interest and informing them that they are not eligible for participation.

Additionally, participants who select any option other than “not at all” on item 9 of the PHQ will receive an email containing links to psychological resources for accessing mental health support. These resources will include https://findahelpline.com/countries/nl and https://www.government.nl/topics/mental-health-services/question-and-answer/help-for-mental-health-problems. These participants will also be excluded from the study.

At the end of the survey, participants will receive instructions for downloading the study mobile phone application, which will also be sent via email for easy reference. The study will be implemented through the TIIM app (Twente Intervention and Interaction Machine; https://www.utwente.nl/en/bmslab/infohub/tiim/; see Fig. 3), a mobile phone application that enables real-time, customized assessments, surveys, and interventions tailored to users’ needs. TIIM will be used to deliver daily notifications, administer EMA questions, provide access to the microinterventions, and collect post-intervention and follow-up assessments when completed through the app. We will not collect passive smartphone-generated data such as GPS location, device usage information, or other automatically generated metadata.

**Fig. 3 fig3:**
[figure not shown]
Design of the TIIM mobile-based app intervention.

Once participants register in the TIIM app and enroll in the study, they will be randomly assigned in a 1:1:1 ratio to one of three groups: RWM, CWM, or the control group. Randomization will be performed using the Study Randomizer software [50]. After enrollment, participants will receive a schedule outlining the microinterventions to be completed during the study. Reminder emails will be sent to encourage participants to download the app and complete enrollment.

In Step 2, participants will begin receiving daily notifications throughout the 7-day intervention period. These notifications will include the scheduled microinterventions and brief EMA questions administered before and after each exercise.

In Step 3, participants will complete the post-intervention assessment one day after the 7-day intervention period. This assessment will be administered through the TIIM app via a notification that will remain available for 24 h. When participants do not complete the post-assessment within this timeframe, a reminder via email will be sent to the email address provided during the baseline assessment, containing a Qualtrics link to the post-assessment survey. This will allow participants a one-week window to complete the survey, starting from the date of their last uncompleted post-assessment notification.

In Step 4, follow-up data will be collected through a notification will be sent via the TIIM app two weeks after the post-assessment. As with the post-assessment, we will implement the same strategy during the follow-up period, including email reminders, to maximize response rates effectively.

### Distal outcomes

2.9

Distal outcomes refer to the broader psychological variables expected to change after the intervention period and at the two-week follow-up. These outcomes include both mental health indicators and values-related variables.

#### Mental health outcomes

2.9.1

Mental health outcomes include:

##### Well-being

2.9.1.1

The Mental Health Continuum-Short Form will be used (MHC-SF; [51]). This 14-item scale measures three types of well-being: emotional well-being (3 items, e.g., “how often did you feel happy?”), social well-being (5 items, e.g., “how often did you feel that people are basically good”), and psychological well-being (6 items, e.g., “how often did you feel confident to think or express your own ideas and opinions?”). Respondents indicate how often during the past week they experienced each feeling on a 6-point scale, ranging from 0 (never) to 5 (every day). The total score is calculated as a sum of the 14 questions. The total score ranges from 0 to 70, with higher scores indicating higher levels of well-being. The original version of the MHC-SF has good reliability and validity in its English version.

##### Meaning in life

2.9.1.2

The Meaning in Life Questionnaire will be used (MLQ, [52]). This 10-item scale measures two facets of meaning in life: the presence of meaning (5 items, e.g., “I understand my life's meaning”), and search for meaning (5 items, e.g., “I am looking for something that makes my life feel meaningful”). Items are rated on a 7-point scale, ranging from 1 (absolutely untrue) to 7 (absolutely true). The presence of meaning score is the sum of items 1, 4, 5, 6, and a reversed item 9, while the search for meaning score is the sum of items 2, 3, 7, 8, and 10; both scores range from 5 to 35, with higher scores indicating a greater presence or search for meaning, respectively. The original version of the MLQ has good reliability and validity in its English version.

##### Depression

2.9.1.3

The Patient Health Questionnaire will be used (PHQ-9; [49]). This 9-item scale measures depressive symptoms (e.g., “Little interest or pleasure in doing things”) during the last week. Items are rated on a 4-point scale, ranging from 0 (not at all) to 3 (nearly every day). The total score is calculated as a sum of the 9 questions. The total score ranges from 0 to 27, with higher scores indicating higher levels of depression. Total sum scores can be interpreted as follows: minimal depression (0 to 4 points), mild depression (5 to 9 points), moderate depression (10 to 14 points), moderately severe depression (15 to 19 points), severe depression (20 to 27 points). The original version of the PHQ-9 has good reliability and validity in its English version.

##### Anxiety

2.9.1.4

The General Anxiety Disorder Scale-7 will be used (GAD-7; [53]). This 7-item scale measures anxiety symptoms (e.g., “Feeling nervous, anxious or on edge”) during the last week. Items are rated on a 4-point scale ranging from 0 (not at all) to 3 (nearly every day). The total score is calculated as a sum of the 7 questions. The total score ranges from 0 to 21, with higher scores indicating higher levels of anxiety. Total sum scores can be interpreted as follows: no symptoms (0 to 4 points), mild (5 to 9 points), moderate (10 to 14 points), and severe symptoms (15 points or more). The original version of the GAD-7 has good reliability and validity in its English version.

##### Ability to adapt

2.9.1.5

The Generic Sense of Ability to Adapt Scale will be used (GSAAS; [54]). This 10-item scale measures the ability to readjust after a personally challenging event (e.g., “I can handle setbacks well”). Items are rated on a 5-point scale, ranging from 1 (not at all) to 5 (completely). The total score is calculated as a sum of the 10 items. The total score ranges from 5 to 50, with higher scores indicating better ability to adapt. The original version of the GSAAS has good reliability and validity in its English version.

#### Values-related outcomes

2.9.2

Values-related outcomes include valued living and values motivational content:

##### Valued living

2.9.2.1

The Engaged Living Scale will be used (ELS-16; [55]). This 16-item scale measures valued living (VL, items 1-10, e.g., “I have values that give my life more meaning”) and life fulfillment (LF, items 11-16, e.g., “I live the way I always intended to live”) during the last week. Items are rated on a 5 point scale, ranging from 1 (completely disagree) to 5 (completely agree). The total subscales scores are calculated as a sum of the items. Total subscale scores range from 10 to 50 in the VL subscale, and from 6 to 30 in the LF subscale. The total scale score is calculated as a sum of the items. Total scale scores range from 16 to 80, with higher scores indicating higher engaged living. The original version of the ELS-16 has good reliability and validity in its English version.

The Multidimensional Psychological Flexibility Inventory will be used (MPFI; [56]). This 60-item scale measures twelve independent dimensions of the Hexaflex model. For this study, 4 dimensions of the MPFI will be measured with reference to the past week: Contact with values (5 items; e.g., “I was very connected with what is important to me and to my life”); Committed Action (5 items; e.g., “Even in the face of failure I did not stop pursuing what is important to me”; Lack of Contact with Values (5 items; e.g., “Often my priorities and values were left behind in my daily life”; Inaction (5 items; e.g., “Often negative emotions paralyzed me and prevented me from acting”). Items are rated on a 6-point scale, ranging from 1 (Never true) to 6 (Always true). The total subscales scores are calculated as a sum of the 5 items. The total subscales scores range from 5 to 30, with higher scores indicating higher levels of each dimension. The original version of the MPFI has good reliability and validity in its English version.

##### Values motivational content

2.9.2.2

The Higher-Order-Value Scale-17 will be used (HOVS17; [57]). This 17-item scale measures the 4 higher-order values from the Schwartz's TBHV [2]: openness to change (5 items; e.g., “It is important to her/him to develop her/his own opinions”), self-enhancement (4 items; e.g., “It is important to her/him to show that her/his performance is better compared to the performance of other people”), conservation (3 items; e.g., “It is important to her/him to maintain traditional values and ways of thinking”) and self-transcendence (5 items; e.g., “It is important to her/him to care for nature”). Items are rated on a 6 point scale, ranging from 1 (not like me at all) to 6 (very much like me). The total subscale scores are calculated as a sum of the items. The total subscales scores range from 5 to 25 for openness to change; from 4 to 24 for self-enhancement; from 3 to 18 for conservation; and from 5 to 25 for self transcendence; with higher scores indicating higher importance of each value dimension. The original version of the HOVS17 has good reliability and validity in its English version.

#### Baseline MIA

2.9.3

MIA will be calculated by combining the scores of imagery controllability and vividness:

##### Controllability

2.9.3.1

The Test of Visual Imagery Control will be used (TVIC; [[58], [59], [60]]). This 12-item scale measures the ability to control mental images (e.g., “Can you see a car standing in front of a house?”). Items are rated on a 7-point scale, ranging from 0 (cannot see the image at all) to 6 (very easy). The total score is calculated as a sum of the 12 items. The total score ranges from 0 to 72, with higher scores indicating better controllability. The original version of the TVIC has good reliability and validity in its English version.

##### Vividness

2.9.3.2

The Shortened Questionnaire Upon Mental Imagery (SQMI), a shortened version of Betts’ [61] original Questionnaire Upon Mental Imagery, will be used [62]. This 35-item scale measures vividness of mental imagery on seven sensory modalities: visual, auditory, cutaneous, kinesthetic, olfactory, gustatory and organic (e.g., visual image of “The sun sinking below the horizon”). Items are rated on a 7-point scale, ranging from 1 (No image present at all) to 7 (Perfectly clear). The total score is calculated as a sum of the 35 items. The total score ranges from 35 to 245, with higher scores indicating higher vividness of imagery. The original version of the SQMI has good reliability and validity in its English version. Table 1 provides an overview of the distal outcomes.

**Table 1 tbl1:** Study variables, questionnaires and assessment time points.

Variable	Questionnaire	S	T1	T2	T3
Well-being	MHC-SF	-	x	x	x
Meaning in life	MLQ	-	x	x	x
Depression	PHQ-9	x	-	x	x
Anxiety	GAD-7	-	x	x	x
Ability to adapt	GSAAS	-	x	x	x
Valued living	ELS-16	-	x	x	x
	MPFI	-	x	x	x
Values content	HOVS17	-	x	x	x
Imagination control	TVIC	-	x	-	-
Imagination vividness	BETT	-	x	-	-

*Note*. S: screening, T1: baseline, T2: post-intervention, T3: two-week follow-up.

### Proximal outcomes

2.10

Proximal outcomes will be measured before and after completing the microinterventions. The following proximal outcomes will be measured daily using visual analog scales (VAS) ranging from 0 to 100:

#### Momentary mental health states

2.10.1

Momentary mental health states will include general well-being (“At this moment, what is your level of well-being?”). Following de Vries et al. [63], affective hedonic well-being will be assessed with the item “How happy do you feel right now?”, and cognitive hedonic well-being with the item “At this moment, to what extent are you satisfied with your life?”. Eudaimonic well-being will be assessed using item 14 from the MHC-SF [51], selected because purpose in life is a core component of eudaimonic well-being [64]: “At this moment, to what extent are you feeling that your life has a sense of direction or meaning?”. Depression and anxiety will be assessed using items adapted from the ultra-brief PHQ-4 [65]. Depressive symptoms will be assessed with the items “At this moment, to what extent are you feeling little interest or pleasure in doing things?” and “At this moment, to what extent are you feeling down, depressed, or hopeless?”. Anxiety symptoms will be assessed with the items “At this moment, to what extent are you feeling nervous, anxious, or on edge?” and “At this moment, to what extent are you unable to stop or control worrying?”.

#### Momentary valued living processes

2.10.2

Because momentary assessment tools for valued living processes remain limited, we developed study-specific EMA items to assess several dimensions of valued living. These included values clarity (“At this moment, how easy is it for you to identify the values that drive your life?”), values awareness (“In the last 24 h, to what extent have you been consciously aware of your values?”), frequency of valued actions (“In the last 24 h, how many of your actions have been aligned with your values?”), awareness during valued actions (“How aware were you, while doing them, that you were acting according to your values?”), and intention to engage in valued actions (“To what extent do you intend to take actions aligned with your values in the following hours?”).

#### Quality of values practice

2.10.3

The quality of values practice will be measured after the 50th birthday party with the Values Practice Quality Scale (VPQS). Considering that compassion and values-based practices share common elements, such as the use of imagery and bodily sensations, we adapted the Compassion Practice Quality Scale (CPQS) by Navarrete et al. [42] and constructed the VPQS, particularly for this study. The adapted VPQS was based on values literature and incorporates expressions specifically aligned with the values process, ensuring greater relevance and applicability. This 10-item scale measures the values practice quality with two subscales: imagery (items 1,2,3,4,6, and 8), e.g., “During the exercise, I had a lot of difficulty choosing the elements that made up the mental scene) and somatic (items 5,7,9, and 10) e.g., “During the exercise, I noticed feelings of vitality and expansion in my body”. Items are rated on a scale from 0 to 100, indicating the percentage of time their experience aligns with each statement. Higher scores indicate better practice quality (fewer difficulties), except for negative items (items 1, 2, 3, 4, 6, and 8). CPQS has good reliability and validity in its version in Spanish [42]. Reliability and validity of the VPQS remains to be tested. A short 4-item daily questionnaire for assessing the quality of values practice after the 3-min wake-up will be created by selecting the items with the highest factor loadings from the original scale.

Table 2 provides an overview of the proximal outcomes.

**Table 2 tbl2:** Study variables, EMA items and assessment time points.

Variable	EMA items	50th birthday party		3-min wake-up		Friendly reminder
		Pre	Post	Pre	Post	Pre
Well-being	At this moment, what is your level of well-being?	x	x	x	x	-
	How happy do you feel right now?	x	x	x	x	-
	At this moment, to what extent are you satisfied with your life?	x	x	x	x	-
	At this moment, to what extent are you feeling that your life has a sense of direction or meaning to it?	x	x	x	x	-
Depression	At this moment, to what extent are you feeling little interest or pleasure in doing things?	x	x	x	x	-
	At this moment, to what extent are you feeling down, depressed or hopeless?	x	x	x	x	-
Anxiety	At this moment, to what extent are you feeling nervous, anxious, or on edge?	x	x	x	x	-
	At this moment, to what extent are you not being able to stop or control worrying?	x	x	x	x	-
Values clarity	At this moment, how easy is it for you to identify the values that drive your life?	x	x	x	x	-
Values awareness	In the last 24 h, to what extent have you been consciously aware of your values?/Since the last notification, to what extent have you been aware of your values? (for friendly reminders notifications)	x	-	x	-	x
Frequency of valued actions	In the last 24 h, how many of your actions have been aligned with your values?	x	-	x	-	-
Awareness during valued actions	And how aware were you, while doing them, that you were acting according to your values?	x	-	x	-	-
Intention to engage in valued actions	To what extent do you INTEND to take actions aligned with your values in the following hours?	x	x	x	x	-
Quality of values practice	1. During the practice, I had great difficulty choosing the elements that shaped up the mental scene that I was using to clarify my values.	-	x	-	-	-
	2. During the practice, I had many difficulties constructing the mental scene that I was using to connect with my values.	-	x	-	x	-
	3. During the practice, I had great difficulty holding the mental scene that I was using to clarify my values.	-	x	-	-	-
	4. During the practice, I had a hard time manipulating the mental scene that I was using to connect with my values.	-	x	-	x	-
	5. During the practice, I managed to generate a sense of meaning and significance towards my life.	-	x	-	x	-
	6. During the practice, I had great difficulty seeing clearly and in detail the mental scene that I was using to clarify my values.	-	x	-	-	-
	7. During the practice, I felt that I was completely within the visualization, forgetting that I was in this room.	-	x	-	-	-
	8. During the practice, I self-criticized myself for not being able to clarify my values.	-	x	-	-	-
	9. During the practice, I noticed a sense of vitality or expansion in my body.	-	x	-	x	-
	10. During the practice, I perceived a great connection and sense of closeness with the mental scene that I was using to clarify my values.	-	x	-	-	-

*Note*. Pre = pre-microintervention; Post = post-microintervention.

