### Statistical analysis

2.11

Data will be processed and analyzed with R 4.4.2 [66] or newer and the RStudio interface [67].

First, to test proximal and trajectory effects with and without photography, as well as the moderating role of quality of practice (Objectives 1.a, 1.b, 2, and 3), linear mixed-effects models will be fitted using the *lmerTest* package [68]. Separate models will be fitted for each proximal outcome within each microintervention as the dependent variables. For the 50th birthday party microintervention, participants from the RWM and CWM conditions will be pooled for the pre-post analysis, as the photography component in the CWM condition is introduced only after the post-microintervention EMA. Thus, time (pre- vs. post-microintervention), quality of practice, and their interaction will be entered as fixed-effect predictors. For values awareness, frequency of valued actions and awareness during valued actions, which require time and opportunity to occur or be noticed in daily life, change will be examined using the next available EMA assessment, collected the following day before the 3-min wake-up microintervention. Given that this assessment occurs after the photography task, models including condition will be conducted to examine potential RWM-CWM differences. For the 3-min wake-up microintervention, condition (RWM, CWM), time (pre- vs. post-microintervention), day (from 1 to 6), quality of practice, and their interactions will be entered as fixed-effect predictors. For the friendly reminder microintervention, condition (RWM, CWM, control), time (pre- vs. post-microintervention), day (from 1 to 6), quality of practice, and their interactions will be entered as fixed-effect predictors. Additionally, to examine the combined effect of the 3-min wake-up and friendly reminder microinterventions across the intervention period, linear mixed-effects models will be fitted using the variables assessed in the first EMA assessment of each day as dependent variables. This approach will allow us to examine whether values awareness, frequency of valued actions and awareness during valued actions change across repeated daily engagement with the intervention. Condition (RWM, CWM, control), day (from 1 to 6), and their interaction will be entered as fixed-effect predictors. Participant will be entered as a random-effect predictor in all models. Models will be estimated using restricted maximum likelihood (REML). Under the missing at random (MAR) assumption, all available data will be used, so participants with incomplete EMA data will still contribute to the analyses based on the observations they provide.

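### The first friendly-reminder reading of each day follows the wake-up and no same-day reminder, and the reminder model has no prompt-position term, so its estimate mixes the wake-up effect with the reminder effect

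*Protocol article*

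**What the plan says.** Table 2 (Section 2.10.3) gives the friendly reminder a Pre column only. The single item marked there is values awareness, worded for these prompts as "Since the last notification, to what extent have you been aware of your values? (for friendly reminders notifications".

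Section 2.7 sets the schedule. The wake-up module "will be available from 6:00 a.m. to 12:00 p.m". The reminder "will be available from 3:00 p.m. to 5:00 p.m., from 6:00 p.m. to 8:00 p.m., and from 9:00 p.m. to 11:00 p.m". Both run on the same six days, so a wake-up notification precedes the first reminder every time.

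Section 2.11 states: "Separate models will be fitted for each proximal outcome within each microintervention as the dependent variables". The reminder model is then specified: "For the friendly reminder microintervention, condition (RWM, CWM, control), time (pre- vs. post-microintervention), day (from 1 to 6), quality of practice, and their interactions" are the fixed effects, with participant as the random effect. A different model, fitted to the first assessment of each day, covers the combined effect of the wake-up and the reminders. Section 2.6 gives the control group the pre-questions and none of the exercises.

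**The concern.** The plan presents the reminder model as specific to one exercise: it stands apart from the wake-up model and from the combined-effect model, and the Discussion says the study compares the exercises. The outcome does not have that specificity at every prompt. The first reading of the day is taken before any reminder that day, and its recall period starts at the wake-up notification. Counting it as a reminder outcome brings the wake-up into the reminder estimate.

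The model offers no way to separate the two. Prompt position is not among its terms, and the pre/post factor it does list has no post reading for this item. The analyst must therefore invent a coding, and that choice determines whether the wake-up is added to the reminder effect or subtracted from it. At stake is the reported effect of one of the trial's three exercises, and whether photography changes it, since Section 2.5.2 adds photographs to both the wake-up and the reminder.

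**Working it through.** The protocol states no figure on this point, so there is nothing to reproduce. The counts come from Section 2.7; the effect sizes below are assumptions.

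**Exposure before each reading (from the schedule)**

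| Prompt | Answered | Previous notification | Same-day reminder already received? |
|---|---|---|---|
| 1 | 15–17 h | wake-up, 6–12 h | no |
| 2 | 18–20 h | reminder 1, 15–17 h | yes |
| 3 | 21–23 h | reminder 2, 18–20 h | yes |

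- Readings per participant: 3 × 6 days = 18.
- Readings with no same-day reminder: 1 × 6 = 6, and 6/18 = 33%.
- The third reminder of a day (also 6 of 18) is followed by no reading of this item; only the next morning's 24 h item can pick it up.

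**Expected active-minus-control difference**

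Let W be the wake-up effect present at prompt 1, R the reminder effect, and c (0 to 1) the fraction of W still present at prompts 2 and 3.

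- Prompt 1: W
- Prompts 2 and 3: R + cW

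**What each possible coding estimates**

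- Three prompts pooled: [W + 2(R + cW)]/3 = (2R + W(1+2c))/3
- Prompt 1 as pre, prompts 2–3 as post: (R + cW) − W = R − (1−c)W
- Chained, each prompt being post for the previous reminder and pre for the next: (R + cW) − [W + (R + cW)]/2 = (R − (1−c)W)/2

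| W | R | c | Pooled | Prompt 1 as pre | Chained |
|---|---|---|---|---|---|
| 10 | 0 | 0 | 3.3 | −10 | −5 |
| 10 | 0 | 0.5 | 6.7 | −5 | −2.5 |
| 10 | 0 | 1 | 10 | 0 | 0 |
| 0 | 10 | any | 6.7 | 10 | 5 |
| 10 | 10 | 0 | 10 | 0 | 0 |
| 10 | 10 | 0.5 | 13.3 | 5 | 2.5 |

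Pooling returns R only if W(1+2c) = R. Prompt 1 as pre returns R only if W = 0 or c = 1. With W and R not negative, chaining returns R only if R = 0 and either W = 0 or c = 1.

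**Simulation check.** Random-intercept models were fitted to simulated trials of 159/3 = 53 per arm, 18 readings each, person and residual SDs both 15 (assumed), 40 trials per scenario.

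| W, R, c | Pooled, mean | Condition × time (prompt 1 as pre), mean |
|---|---|---|
| 10, 0, 0 | 3.5 | −9.8 |
| 0, 10, 0 | 7.2 | 9.9 |
| 10, 10, 0 | 10.6 | −0.1 |
| 10, 0, 0.5 | 6.7 | −4.8 |

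The simulation error of a pooled mean is about √[237.5 × (1/53 + 1/106)]/√40 = 0.41, where 237.5 = 225 + 225/18. The largest gap from the formula, 10.63 − 10 = 0.63, is about 1.5 such errors.

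**Cost of using 12 rather than 18 readings.** The SE ratio for a contrast of person means is √{[ICC + (1−ICC)/12] / [ICC + (1−ICC)/18]} = 1.028, 1.013 and 1.009 for ICC 0.3, 0.5 and 0.6.

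**The case against.** The strongest reply is that this is a condensed article: how time is coded and how prompts are indexed may sit in the preregistration or a full analysis plan. That stands for the coding. It does not dispose of the point, because Section 2.11 lists the model's terms, prompt position is not among them, and none of the three codings above isolates the reminder outside special cases.

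Several stronger readings are tempting, and the documents do not support them:

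- **The model credits the wake-up to the reminder and dilutes real reminder effects.** That follows only if the prompts are pooled. If prompt 1 is the pre value, the wake-up is subtracted, and with W = 0 there is no dilution. Even when pooled, the two errors can cancel (W = R = 10, c = 0 gives 10).
- **Each prompt has its own window and exposure.** Only prompt 1 differs. Prompts 2 and 3 share the same nominal window and the same kind of exposure.
- **The look-back is more than twice as long at prompt 1.** Measured from completion it is 3–11 h against 1–5 h, and average look-backs of 7 h against 3 h need assumed uniform answer times. Measured from sending, taking the 11:00 wake-up chaser as the last notification and reminders as sent when their windows open, it is 4–6 h against 3–5 h, or 5 h against 4 h at the midpoints. In any case control shares the nominal schedule, so unequal look-back alone does not bias the comparison of conditions.

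It is also fair to say that no recoding fully isolates the reminder, because no arm receives reminders without the wake-up.

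**Conclusion.** The point holds in limited form. One third of the readings assigned to the friendly reminder cannot reflect a same-day reminder, and the model as listed cannot set them apart. The resulting estimate is a mixture of W and R whose direction of bias depends on an unstated coding choice. The 6 of 18 rests on the protocol's own schedule alone. The sizes do not: W, R and c are illustrative, equal response at the three prompts is assumed, and W stands for everything active participants carry into the afternoon, including any residue of earlier days' exercises. This should be settled before analysis, but it concerns one momentary item and leaves the distal outcomes untouched.

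**What to change.** In the friendly-reminder model of Section 2.11, replace the pre/post factor with prompt position (1 vs 2–3), and report two contrasts:

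- active against control at prompt 1, as the wake-up effect carried into the afternoon (W);
- active against control at prompts 2–3, as the effect of reminders added to the wake-up (R + cW).

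Do not report the condition × prompt-position interaction as the reminder effect. It estimates R − (1−c)W, so with W = R = 10 and c = 0 it returns 0 for a reminder that works. State that a stand-alone reminder effect cannot be isolated in this design. One practical note: quality of practice is recorded only after exercises that control does not do, so the contrasts with control need a version of the model without that term.

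The change is to analysis wording and needs no new data, provided each reading is stored with the prompt it answered. The costs are the 1–3% larger standard error for the reminder contrast, and that any wake-up effect lasting into the evening remains in the prompts 2–3 contrast.
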